### Secondary Outcomes

Secondary analyses focus on indicators of drug use and severity (primary outcomes in the parent study). Drug use is operationalized in 2 ways. First, using TLFB interview data, the quantity of drug use will be operationalized using the total number of instances reported during the assessment period. We will examine cannabis and other illicit drug use frequency separately. Urine assay will corroborate the self-report. In instances where urine results signal the use of drugs not reported, we will use data from the objective indicator. Second, drug use severity will be assessed using the Drug Abuse Screening Test [52] total score.

### Participant Timeline

See Figure 1 for a timeline of participant flow through the study.

**Figure 1 figure1:**
[figure not shown]
Timeline of participation. ACT: assertive communication training; CHTC: couples HIV testing and counseling; STI: sexually transmitted infection; SUC: substance use calendar; TLFB: timeline followback.

### Sample Size

Power to detect significant between-group differences in primary outcomes was calculated using the PASS program (version 2022; NCSS, LLC). Analyses focused on power to detect a significant between-group difference at any 1 follow-up time point. Results from the tests for difference between 2 Poisson rates in a cluster randomized design module indicated the study had power of >0.80 to detect a 20% or greater reduction in the rate of CAS with casual partners. This estimate assumed a sample of 200 couples with equal allocation to condition, and models were tested with based rates of 2-4 instances of CAS with a casual partner among the control (individual HIV testing and counseling) condition. Results from the tests for 2 proportions in a cluster-randomized design suggested proposed study has power of >0.80 to detect a 22% reduction in the proportion of reporting main partner TRB, assuming a sample of 200 couples and a 70% base rate in the control condition.

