##### Primary Analyses of Intervention Effects

The primary hypothesis is that CHTC retesting will be associated with significant reductions in sexual HIV TRB (primary) outcomes compared to individual HIV testing. Using procedures similar to our previously published studies [54], outcome analyses will be conducted in a multilevel modeling framework. Analyses will use full-information maximum likelihood estimation and specify a negative binomial distribution consistent with the count nature of primary outcomes. The appropriateness of a Poisson distribution will be determined by inspection of the significance of the dispersion parameter in negative binomial models. This accounts for the nesting of individuals within couple. Because randomization occurs at the couple level, condition is a level 2 variable. The effect of the intervention will be evaluated by examining the regression coefficient (and associated *P* value). Separate models will be calculated to predict outcomes at 3- and 6-month follow-ups (with Bonferroni correction for repeated nonorthogonal tests). Mplus (Muthén and Muthén) accommodates count and dichotomous outcomes within the multilevel modeling context. Analysis of secondary outcomes will follow analogous analytic procedures.

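### The stated power of more than 0.80 for casual-partner CAS does not hold at base rate 2 under the planned Bonferroni correction: it is at most about 0.77

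*Protocol article*

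**What the plan says.** The Sample Size section of the protocol article frames the calculation one visit at a time: "Analyses focused on power to detect a significant between-group difference at any 1 follow-up time point". For outcome 1, the number of CAS acts with a casual partner without PrEP, it claims "power of >0.80 to detect a 20% or greater reduction in the rate of CAS with casual partners". On the number of couples it says: "This estimate assumed a sample of 200 couples with equal allocation to condition". On the control rates it says that "models were tested with based rates of 2-4 instances of CAS with a casual partner among the control". For outcome 2, main-partner transmission risk behaviour (TRB), it claims "power of >0.80 to detect a 22% reduction in the proportion of reporting main partner TRB". The inputs for that second claim are given as "assuming a sample of 200 couples and a 70% base rate in the control condition". Both calculations use cluster-randomized PASS modules. The section gives no alpha, no sidedness and no within-couple correlation.

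The section on Primary Analyses of Intervention Effects says how significance will be judged: "Separate models will be calculated to predict outcomes at 3- and 6-month follow-ups (with Bonferroni correction for repeated nonorthogonal tests"). Within each model, "The effect of the intervention will be evaluated by examining the regression coefficient (and associated *P* value").

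**The concern.** A power figure should describe the test that will be run. The power section considers one comparison at one visit and does not mention a correction. The analysis section applies a correction over the two visits, so each comparison must meet a stricter threshold than the conventional 0.05. If the power was computed without that correction, the chance of meeting the threshold at a given visit is lower than readers are told. A null result at low base rates could then be taken as coming from an adequately powered comparison when it did not.

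**Working it through.** **Inputs from the protocol article.** 200 couples allocated equally gives 100 couples per arm. The outcomes are individual-level, so there are 200 men per arm in clusters of two. Outcome 1 has control rates of 2 to 4 and a 20% reduction. Outcome 2 has a control proportion of 0.70 and a 22% reduction.

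**Assumptions, because the article does not state them.** Tests are two-sided. Overall alpha is 0.05, so Bonferroni over two visits gives 0.025 per test. The within-couple correlation ρ is shown over a range, with design effect 1 + ρ. There is no attrition and no overdispersion. Critical values are 1.960 (0.05) and 2.241 (0.025); 0.842 is added for 80% power.

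**Outcome 1, base rate 2 (2 v 1.6).**

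z = 0.4 / √[(2 + 1.6)/200 × (1 + ρ)], which is 2.981 at ρ = 0.

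- *The plan's own figure, at uncorrected 0.05:* Φ(2.981 − 1.960) = 0.846 at ρ = 0. Power stays at 0.80 or more up to ρ = (2.981/2.802)² − 1 = 0.13. The stated figure therefore reproduces at 0.05 with a small correlation.
- *At 0.025:* Φ(2.981 − 2.241) = 0.770 at ρ = 0. Log-rate and square-root versions and a simulation all fall within 0.002 of this. Reaching 0.80 would need ρ = (2.981/3.083)² − 1 = −0.065, a negative correlation.

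| ρ | Power at 0.05 | Power at 0.025 |
|---|---|---|
| 0 | 0.85 | 0.77 |
| 0.1 | 0.81 | 0.73 |
| 0.2 | 0.78 | 0.68 |
| 0.3 | 0.74 | 0.65 |
| 0.5 | 0.68 | 0.58 |

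At 0.025 and ρ = 0, 80% power at base rate 2 needs 3.083² × 3.6/0.16 ≈ 214 couples. With 200 couples it needs a base rate of at least about 2.14. Solving the same formula for the reduction r, 2r / √[(4 − 2r)/200 × (1 + ρ)] = 3.083, gives a detectable reduction of 20.6% at ρ = 0 and 25.0% at ρ = 0.5.

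**Outcome 1, base rates 3 and 4, at 0.025.** At ρ = 0, z = 0.6/√(5.4/200) = 3.651 and 0.8/√(7.2/200) = 4.216, giving power of 0.92 and 0.98. Power stays at 0.80 or more up to ρ = (3.651/3.083)² − 1 = 0.40 and (4.216/3.083)² − 1 = 0.87.

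**Outcome 2, 22% read as relative (0.70 to 0.70 × 0.78 = 0.546).**

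z = 0.154 / √[(0.2100 + 0.2479)/200 × (1 + ρ)], which is 3.22 at ρ = 0.

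- At 0.05: power is 0.90 (0.89 with pooled variance) at ρ = 0, and stays at 0.80 or more up to ρ = 0.32 (0.30 pooled).
- At 0.025: power is 0.84 (0.83 pooled) at ρ = 0. It falls below 0.80 once ρ exceeds 0.09 (0.07 pooled), and is 0.72 (0.71 pooled) at ρ = 0.3.

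**Outcome 2, 22% read as points (0.70 to 0.48).** At 0.025, power is 0.84 (0.83 pooled) even at ρ = 1, so it never falls below 0.80.

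**The case against.** The article is condensed, and it fixes neither alpha, sidedness nor the family of tests. The 0.77 therefore rests on a conventional reading. The hypothesis is directional, and at one-sided 0.025 power at base rate 2 would be 0.846 with zero correlation. That is a fair caution, but nothing in the article mentions one-sided testing.

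The wording about any one follow-up could be taken to mean a difference at either visit. That power, at 0.025 per test and zero within-couple correlation, would be about 0.83 to 0.95 for between-visit correlations from 0.9 down to 0. The PASS modules named make a single comparison of two rates or two proportions, however, and do not compute it.

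The strongest objections limit how far the point reaches, and they stand:

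- A reader might infer that both primary outcomes fall short. The documents do not support that. Outcome 2 still exceeds 0.80 at 0.025 with zero correlation, and under the points reading it does so at any correlation. The relative reading is more likely: it matches the 20% reduction beside it, and 22% relative is what 0.80 power gives at 0.05 with a correlation of about 0.3. It is not established.
- A reader might argue that sex between main partners is a shared act, so the correlation must be well above 0.09. Outcome 2 is defined for each respondent and also depends on his own PrEP use and, in part, on casual partners. These can differ within a couple, and the article gives no correlation.
- A reader might infer an arithmetic error. The stated figures reproduce at an uncorrected 0.05 with a modest correlation. The problem is a mismatch between two sections.
- With zero correlation, the shortfall is modest and confined to the low end of the base-rate range.

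**Conclusion.** The power claim for outcome 1 does not hold over its whole stated range at the level the analysis will use. At base rate 2, power is at most about 0.77 against a claim of more than 0.80, and any positive within-couple correlation lowers it. This assumes two-sided 0.05 overall, split over two visits. It is an upper bound on that footing: the planned analysis starts from a negative binomial model, and overdispersion or attrition would reduce power. If the correction also covered the two primary outcomes (0.0125 per test), power at base rate 2 would be 0.69 at zero correlation. Base rates 3 and 4 are sound except at larger correlations. For outcome 2 the conclusion is conditional: power falls below 0.80 only if 22% is relative and the correlation exceeds about 0.07 to 0.09.

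**What to change.** In the Sample Size section, restate both power figures at the per-test alpha implied by the analysis section (0.025 under the assumptions here), and state the within-couple correlation used. Give base rate 2 its own figure, at most about 0.77, or restate its detectable reduction as about 21% at zero correlation, rising to 25% at 0.5. Write outcome 2 as 70% to x%, so that the 22% is clearly relative or absolute. If the correction over visits is changed, use the per-test alpha that then applies.

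The cost is a rerun of the power program, a few changed sentences and slightly less favourable figures. Trial conduct and the planned analysis do not change.

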### Primary Outcomes

Primary analyses focus on 2 (individual-level) behavioral indicators of HIV transmission risk: (1) the number of CAS acts with a casual partner in the absence of the respondent taking PrEP and (2) CAS with a serodiscordant main partner who is not virally suppressed or concurrent CAS between main and casual partners in the absence of the respondent taking PrEP. The availability of day-level data generated by the timeline followback (TLFB) assessment allows for an examination of event-driven PrEP dosing as well as overall day-level adherence. Self-reported sexual behavior will be corroborated with results from bacterial STI (gonorrhea and chlamydia) testing. In instances where these indicators of HIV TRB suggest CAS with a casual (or main) partner occurred but was not reported, we will use data from the objective indicator.

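### The power above 0.80 claimed for the first primary outcome is not for the planned Bonferroni-corrected negative binomial test, and that test does not reach it at a control rate of 2

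*Protocol article*

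**What the plan says.** The Sample Size section makes two power statements.

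- First primary outcome: "Results from the tests for difference between 2 Poisson rates in a cluster randomized design module indicated the study had power of >0.80", specifically "to detect a 20% or greater reduction in the rate of CAS with casual partners". On the inputs: "This estimate assumed a sample of 200 couples with equal allocation to condition". For the control arm, the section adds that "models were tested with based rates of 2-4 instances of CAS with a casual partner".
- Second primary outcome: power above 0.80 for a 22% reduction from a 70% control proportion, again with 200 couples.

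Both concern a single visit: "Analyses focused on power to detect a significant between-group difference at any 1 follow-up time point". Neither comes with an alpha, a sidedness, an ICC or a dispersion.

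The section Primary Analyses of Intervention Effects says that the models will "specify a negative binomial distribution consistent with the count nature of primary outcomes", with Poisson considered after inspecting the dispersion parameter. On multiplicity: "Separate models will be calculated to predict outcomes at 3- and 6-month follow-ups (with Bonferroni correction for repeated nonorthogonal tests"). The Primary Outcomes section defines the first outcome as "the number of CAS acts with a casual partner in the absence of the respondent taking PrEP".

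**The concern.** The power statement and the planned test differ on three points.

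- **Alpha.** The test is corrected over two visits. The power statement mentions no correction.
- **Variance.** The starting model is negative binomial. The power module is for Poisson rates.
- **Endpoint.** The outcome counts only acts without PrEP. The power text does not say whether its base rate carries that restriction.

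Each point, if real, makes the quoted power too high. The trial is meant to inform retesting guidance, so a null result would be read against a claimed power above 0.80 that the planned test may not have.

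**Working it through.** **Inputs from the article.** 200 couples allocated equally, so 100 couples or 200 men per arm in clusters of 2. Rate ratio 0.80. Control rate 2 to 4. Second outcome: 70% in the control arm and a 22% reduction.

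**Assumptions, because the article is silent.** Two-sided test. Bonferroni over the two visits, so 0.05/2 = 0.025 per visit. ICC from 0 upward. Dispersion k in variance = λ + kλ². All 200 couples are taken as analysed.

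**Formula for the rates.** With design effect DE = 1 + ICC for pairs,

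power = Φ( (λ1 − λ2) / √[DE·(V1 + V2)/200] − z ), where V = λ + kλ².

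The critical value z is 1.960 at 0.05 and 2.241 at 0.025.

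**Step 1. Reproduce the stated figure** (Poisson, 0.05, ICC 0). At rate 2: 0.4/√(3.6/200) = 2.981, and Φ(2.981 − 1.960) = 0.846. Rates 3 and 4 give 0.955 and 0.988. So the claim reproduces over the whole range at ICC 0. At rate 2 it holds only up to an ICC of about 0.13.

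**Step 2. Apply the correction only** (Poisson, 0.025).

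| Control rate | ICC 0 | ICC 0.2 | Largest ICC with power 0.80 |
|---|---|---|---|
| 2 | 0.770 | 0.684 | none (below 0.80 at ICC 0) |
| 3 | 0.921 | 0.863 | about 0.40 |
| 4 | 0.976 | 0.946 | about 0.87 |

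At rate 2, Φ(2.981 − 2.241) = Φ(0.740) = 0.770. In this best case the shortfall is small when expressed as an effect. A reduction of about 20.6% would have 80% power: λ2 = 1.587, and 0.413/√(3.587/200) = 3.08 = 2.241 + 0.842.

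**Step 3. Add dispersion** (0.025, ICC 0).

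| k (assumed) | Rate 2 | Rate 3 | Rate 4 |
|---|---|---|---|
| 0.25 | 0.591 | 0.717 | 0.791 |
| 0.5 | 0.466 | 0.553 | 0.606 |
| 1 | 0.320 | 0.363 | 0.388 |

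Example, rate 2 and k = 0.5: V1 + V2 = 4 + 2.88 = 6.88; 0.4/√(6.88/200) = 2.157; Φ(2.157 − 2.241) = 0.466. A simulation of gamma-Poisson counts (4,000 runs) gave 0.468 here and 0.605 at rate 4.

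The k at which power reaches 0.80 solves (λ1 − λ2)²·200/(2.241 + 0.842)² = λ1 + λ2 + k(λ1² + λ2²).

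- Rate 3: 7.575 = 5.4 + 14.76k, so k ≈ 0.15.
- Rate 4: 13.467 = 7.2 + 26.24k, so k ≈ 0.24.

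For scale, if 20% of men in each arm could not contribute a countable act and the rest were Poisson, the variance would match k = 0.20/0.80 = 0.25. Men on PrEP could supply such zeros, but the 20% is an assumption.

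Dispersion matters without the correction too. At 0.05, k = 0.5 and ICC 0, power is 0.578, 0.660 and 0.709.

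**Step 4. Second outcome** (two proportions, effective n = 200/DE per arm).

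| Reading of 22% | 0.05, ICC 0 | 0.025, ICC 0 | 0.025, ICC 0.2 | 0.025, ICC 1 |
|---|---|---|---|---|
| Relative, 70% to 54.6% | 0.891 | 0.829 | 0.748 | 0.502 |
| Absolute, 70% to 48% | 0.995 | 0.989 | 0.971 | 0.828 |

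**The case against.** The strongest reply is that an omission is not an error. Alpha, sidedness and ICC are unstated and could sit in the full protocol, so it is an inference that the correction was left out. That stands, and it limits the claim.

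Two readings would rescue rate 2 under Poisson variance:

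- A one-sided Bonferroni test at 0.025 gives 0.846 at ICC 0. No one-sided test is stated anywhere.
- The phrase about any one time point could mean significance at at least one visit. At rate 2 and ICC 0 that gives about 0.87 to 0.92 for assumed between-visit test correlations of 0.7 to 0.3. Power at a given visit is the more natural reading. Nor does the other one remove dispersion: with k = 0.5 at rate 2, even independent tests would give 1 − (1 − 0.466)² = 0.715.

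The power module was for a cluster-randomized design, so within-couple correlation may have been included. With pairs, that inflates variance at most twofold, and it does not stand in for dispersion between individuals. The plan also allows a Poisson model if the data support it, so dispersion is provided for rather than asserted.

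A reader might infer that the trial lacks its stated power for both primary outcomes. The article does not support that. The second outcome does not rest on Poisson variance, stays above 0.80 on the absolute reading, and does so on the relative reading at ICC 0. An ICC of about 0.3 makes 22% come out at 0.05 on the relative reading, but this does not show which alpha was used. An ICC of about 0.07 to 0.09 does the same at 0.025, and at 0.3 the first outcome would have only 0.744 at rate 2 even at 0.05.

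A reader might also infer that the base rate of 2 to 4 includes PrEP-covered acts. The power text may simply be shorthand, and the article gives no PrEP share.

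**Conclusion.** The concern holds in limited form. The power statement does not describe the test that will be run.

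- **Control rate 2:** a two-sided, per-visit test at 0.025 has power of at most 0.77. This needs no assumed ICC or dispersion, so the claim fails at the low end of the plan's own range.
- **Control rates 3 and 4:** the claim survives the correction alone at moderate ICC. It fails once k exceeds about 0.15 or 0.24 at ICC 0. These are modest values, but the article gives none.
- **Second outcome:** any loss is conditional on the relative reading and on the ICC.

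The result rests on two-sided testing, a correction by a factor of two, and power meaning power at a given visit. If the correction also spanned the two primary outcomes (0.0125), the Poisson, ICC 0 figure at rate 2 would be Φ(2.981 − 2.498) = 0.69. It is not shown that the correction was omitted by mistake, or that the trial is underpowered throughout.

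**What to change.** Restate power, or preferably the minimum detectable reduction, for the planned test:

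- State the Bonferroni alpha, the number of tests it covers, and the sidedness.
- Use a negative binomial variance. Estimate the dispersion and couple ICC from pooled 4Us data without arm information, and show a range around each.
- Use the base rate of acts without PrEP, as the primary outcome is defined.
- Say whether 22% is relative or absolute.

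As an illustration with assumed k = 0.5, 0.025 and 80% power, the minimum detectable reduction is about 27.8% at rate 2 and 24.2% at rate 4 with ICC 0, or 30.2% and 26.3% with ICC 0.2.

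The cost is a rewritten Sample Size paragraph with less favourable figures. Enrollment, assessments and the analysis model stay as they are.

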## Introduction

### Background

Sexual minority men (SMM), a group that encompasses gay, bisexual, and other men who have sex with men, account for 69% of new HIV infections in the United States [1]. Despite the emergence of novel biomedical prevention options (eg, preexposure prophylaxis [PrEP], postexposure prophylaxis [PEP], and HIV undetectable=untransmittable, or treatment as prevention), this overall rate has changed little over the past decade [2]. The majority (68%) of these new infections occur among SMM under the age of 35 years [2]—a proportion that was largely unchanged in the decade between 2009 and 2019 [2].

Nearly 2 decades of research have indicated that HIV prevention interventions that address the needs of SMM in relationships are an essential component of any comprehensive US national HIV prevention plan. Findings first emerged in the early 2000s, indicating that primary partnerships were often a risk for HIV infection [3-5]. Subsequently, epidemiological modeling estimated that between 35% and 68% of HIV infections among SMM are among main partners [6-8]. Rates of primary partner transmission were particularly high (accounting for between 79% and 84% of new infections) among emerging adult SMM (aged 18-29 years) [6]. More recently, Starks et al [9] found that SMM in nonmonogamous relationships (where sex with outside partners is permitted in some way) engage in condomless anal sex (CAS) with casual partners at rates comparable to those who are single. Although men in monogamous relationships were less likely to engage in CAS with casual partners, those who do have CAS with casual partners report doing so more frequently than nonmonogamous men [9].

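### The power above 0.80 for casual-partner condomless anal sex rests on Poisson variance, but the planned test is negative binomial, and the claim survives only at low dispersion

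*Protocol article*

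**What the plan says.** The Sample Size section powers the first primary outcome, the count of condomless anal sex (CAS) acts with casual partners, as follows.

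- Method and result: "Results from the tests for difference between 2 Poisson rates in a cluster randomized design module indicated the study had power of >0.80".
- Effect: "to detect a 20% or greater reduction in the rate of CAS with casual partners".
- Size: "This estimate assumed a sample of 200 couples with equal allocation to condition".
- Control rate: "models were tested with based rates of 2-4 instances of CAS with a casual partner among the control" condition.
- Time frame: "Analyses focused on power to detect a significant between-group difference at any 1 follow-up time point".

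It reports no dispersion, no within-couple correlation or between-couple variation, and no significance level.

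The section on primary analyses of intervention effects plans multilevel models that "specify a negative binomial distribution consistent with the count nature of primary outcomes". Whether Poisson is adequate is to be judged afterwards from the dispersion parameter. On multiplicity: "Separate models will be calculated to predict outcomes at 3- and 6-month follow-ups (with Bonferroni correction for repeated nonorthogonal tests").

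**The concern.** A Poisson calculation sets each man's variance equal to his mean, apart from clustering. A negative binomial model adds a term that grows with the square of the mean, and the standard error of the rate ratio grows with it. The power figure therefore belongs to a narrower variance model than the test the plan will run.

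The design points to extra-Poisson variation. Under Eligibility Criteria, only one partner in each couple has to report risk. That risk may be with a main partner, and it was reported over 90 days at entry to 4Us, about a year before this trial's randomization. The outcome then counts only casual-partner acts without PrEP, in a 30-day interview window. Many men can be expected to contribute zeros while some contribute many acts.

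At stake is how a null result on a primary outcome is read. If dispersion is moderate, a trial described as having more than 0.80 power for a 20% reduction could miss that reduction about half the time, even with all 200 couples enrolled.

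**Working it through.** **Inputs.** From the Sample Size section: 100 couples and so 200 men per arm, rate ratio 0.80 (ln 0.80 = −0.2231), control mean b = 2 to 4 (3 taken as the midpoint), one time point. Assumed because not stated: two-sided alpha 0.05; dispersion d from 0 to 1, with variance = mean + d × mean²; within-couple correlation (ICC) 0 at first.

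**Formula.** SE² of the log rate ratio = [(1/b + d) + (1/(0.8b) + d)] × (1 + ICC) / 200. Power = Φ(0.2231/SE − 1.960). Setting d = 0 gives Poisson.

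**Step 1: reproduce the stated figure (d = 0).** At b = 2, SE² = (0.5 + 0.625)/200 = 0.005625, SE = 0.0750, z = 2.975 and power = Φ(1.015) = 0.85. At b = 3 and 4, power is 0.95 and 0.99. The claim reproduces over the whole stated range.

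**Step 2: allow dispersion.** Example: at b = 2 and d = 0.5, SE² = (1.0 + 1.125)/200 = 0.010625, SE = 0.1031, z = 2.165 and power = Φ(0.205) = 0.58. All cases at alpha 0.05, ICC 0:

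| d | b = 2 | b = 3 | b = 4 |
|---|---|---|---|
| 0 | 0.85 | 0.95 | 0.99 |
| 0.25 | 0.70 | 0.81 | 0.86 |
| 0.5 | 0.58 | 0.66 | 0.71 |
| 1 | 0.43 | 0.48 | 0.50 |

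Working on the rate-difference scale changes these by at most about 0.01. Simulation (500 trials per setting, negative binomial regression with couple-clustered standard errors) gave 0.70, 0.57 and 0.43 at b = 2, and 0.86, 0.69 and 0.48 at b = 4, for d = 0.25, 0.5 and 1.

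**Step 3: break-even dispersion.** Power 0.80 needs SE = 0.2231/2.8016 = 0.0797, so 200 × SE² = 1.269. Since 1/b + 1/(0.8b) = 2.25/b, the largest allowable d is (1.269 − 2.25/b)/2:

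- b = 2: (1.269 − 1.125)/2 = 0.07
- b = 3: (1.269 − 0.750)/2 = 0.26
- b = 4: (1.269 − 0.5625)/2 = 0.35

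In the control arm the variance-to-mean ratio, 1 + db, is then about 1.14, 1.78 and 2.41.

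**Step 4: what break-even implies.** For a negative binomial count, P(zero) = (1 + db)^(−1/d). This is about 0.15 at b = 2, d = 0.07, and about 0.08 at b = 4, d = 0.35. On that distribution the claim needs roughly 85% to 92% of all control men, both partners included, to report at least one PrEP-free casual act in 30 days. The eligibility rules do not select for that.

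**Step 5: within-couple correlation and alpha.** With ICC 0.2 (assumed), power at b = 2/3/4 is 0.62/0.73/0.80 for d = 0.25, 0.51/0.59/0.63 for d = 0.5 and 0.37/0.41/0.44 for d = 1. At the Bonferroni level of 0.025 with ICC 0, it is 0.59/0.72/0.79, 0.47/0.56/0.61 and 0.32/0.37/0.39. At that level even pure Poisson power at b = 2 is 0.77.

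**Step 6: detectable reduction.** Solving for 0.80 power (alpha 0.05, ICC 0) gives about 25% (d = 0.5) and 30% (d = 1) at b = 2, and 22% and 27% at b = 4.

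**The case against.** Several points on the other side are sound.

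- The plan does not say that it expects overdispersion. It justifies the negative binomial by the outcome being a count and leaves Poisson open. A reader might infer that the authors concede overdispersion, but the text does not support that. The shortfall is conditional on a dispersion the article never gives.
- A reader might infer that any overdispersion pulls power down to 0.4–0.7. It does not. At d = 0.25, power is still 0.81 to 0.86 at rates 3 and 4. Across rates 2 to 4, that span needs d of about 0.5 to 1, a control-arm variance 2 to 5 times the mean.
- A reader might call the stated figure a calculation error. It is not: it reproduces under its own assumptions. The fault is that those assumptions differ from those of the planned test.
- The Background remark about men in monogamous relationships, that "those who do have CAS with casual partners report doing so more frequently than nonmonogamous men", concerns a general comparison of relationship types. It fits a long-tailed count but does not quantify dispersion in this risk-enriched sample.
- The module is for cluster-randomized designs, so some between-couple variation may have been entered, and a condensed article need not report it. The room for it is limited. With two men per couple, solving 99(λ1 − λ2)² / [(λ1 + λ2)/2 + k²(λ1² + λ2²)] = 2.80² for the between-couple coefficient of variation k gives at most about 0.18 at rate 2 and 0.41 at rate 4. Any allowance must have been small at the low end of the stated range.
- Covariate adjustment might recover some power, but the power statement claims no such gain, and the Bonferroni correction works the other way.

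What stands is the mismatch of variance models and the break-even values, neither of which depends on a chosen dispersion scenario.

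**Conclusion.** The concern holds as a mismatch of assumptions between the power statement and the planned test. Power above 0.80 for a 20% reduction, stated for control rates of 2 to 4, needs dispersion of no more than about 0.07, 0.26 or 0.35 at rates 2, 3 and 4. This assumes 200 couples, two-sided 0.05 and no within-couple correlation, and correlation or a stricter alpha lowers those limits. Values near zero are implausible in this design. At dispersion 0.5 to 1, power is about 0.43 to 0.71 across the stated rates.

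The true dispersion is unknown from the document, so the size of the shortfall is a range, not an established figure. The documents do not support saying that the trial is shown to have only 0.4–0.7 power, nor that more couples are required.

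**What to change.** Recompute the power for the first primary outcome under the negative binomial multilevel test that the analysis section specifies. Estimate dispersion and within-couple correlation from the 12-month 4Us timeline followback counts, pooled and blind to arm. The plan already treats these data as this trial's pre-randomization baseline. Because dispersion at follow-up may differ, show a range around the estimate. Replace the statement of power above 0.80 for a 20% reduction with the resulting power, or with the reduction detectable at 0.80 power, and state the dispersion, correlation and alpha used.

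The cost is a short recalculation on data already being collected and one rewritten paragraph. Sample size, test and conduct stay as they are. The downside is that the stated detectable effect will probably look less favourable.

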**Results:**

The CHTC retesting trial launched in January 2023, and enrollment is ongoing. As of February 2024, the study had enrolled 106 eligible participants (n=53 couples).

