**Conclusions:**

Findings from this CHTC retesting study will contribute to knowledge about the benefits associated with regular (repeated) CHTC testing versus routine individual HIV testing for SMM in relationships. The results of this trial will inform CHTC retesting guidance.

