## Results

This study began recruitment in January 2023, and all participant components are projected to end in May 2025. As of December 2023, 102 individuals (51 couples) have enrolled in the CHTC retesting trial.

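### Power is stated at 200 couples, but at the reported enrolment pace and projected end date the trial would randomize only about 62 to 91

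*Protocol article*

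**What the plan says.** Sample Size bases both power statements on 200 couples: "This estimate assumed a sample of 200 couples with equal allocation to condition". For outcome 1, the count of condomless anal sex (CAS) acts with casual partners, it claims "power of >0.80 to detect a 20% or greater reduction in the rate of CAS with casual partners", tested over "based rates of 2-4 instances of CAS with a casual partner among the control" condition. For outcome 2 it claims "power of >0.80 to detect a 22% reduction in the proportion of reporting main partner TRB", from a 70% base rate and again with 200 couples. It states no ICC and no alpha, and does not say whether the 22% is relative or absolute.

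On accrual, the main-text Results say "As of December 2023, 102 individuals (51 couples) have enrolled in the CHTC retesting trial", and the Abstract says "As of February 2024, the study had enrolled 106 eligible participants (n=53 couples". Both give a January 2023 start. The main-text Results add that "all participant components are projected to end in May 2025". Trial Design sets follow-ups at 3 and 6 months. Eligibility Criteria admits only couples who complete the parent (4Us) trial's 12-month visit, are still together and both agree to enrol.

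The article gives no revised target and no accrual projection, and the limitations in the Discussion do not mention a shortfall.

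**The concern.** A reader who puts the enrolment counts beside the end date finds far too little time left for 200 couples at the pace so far. The power statement is nevertheless printed without qualification, after 14 months of accrual data were available. The Abstract's Conclusions say "The results of this trial will inform CHTC retesting guidance". If the final sample is less than half the planning figure, a non-significant result could be taken as coming from a trial with more than 80% power when it did not.

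**Working it through.** **Accrual**

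Inputs from the Abstract, Results and Trial Design: start January 2023; 51 couples by December 2023; 53 by February 2024; end May 2025; 6 months of follow-up.

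- Last randomization: May 2025 minus 6 months = about November 2024, so about 9 months remain after February 2024.
- Observed pace: 53/14 = 3.79 per month overall; 51/12 = 4.25 in 2023; 2/2 = 1 in the last two months.
- Projected total: 53 + 9 × 3.79 = 87; 53 + 9 × 4.25 = 91; 53 + 9 × 1 = 62.
- Pace needed for 200: (200 − 53)/9 = 147/9 = 16.3 per month, and 16.3/3.79 = 4.3 times the average.
- The counts are dated only by month. Taking 51 couples over 11 months gives 4.64 per month and a total of 95.
- Enrolling until May 2025 with no time for follow-up would give only 53 + 15 × 3.79 = 110 to 53 + 15 × 4.64 = 123.

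**Power formulas**

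Assumptions: two-sided alpha 0.05, ICC 0 to 0.3, no dropout. With two men per couple and equal allocation, the effective number of men per arm is n = couples/(1 + ICC).

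- Outcome 1, Poisson rates λ1 and λ2 = 0.8 λ1: power = Φ[(λ1 − λ2)/√((λ1 + λ2)/n) − 1.96].
- Outcome 2, pooled-variance test of proportions: power = Φ[(d − 1.96 √(2p̄(1 − p̄)/n)) / √((p1(1 − p1) + p2(1 − p2))/n)], where d = p1 − p2 and p1 = 0.70. The relative reading gives p2 = 0.70 × 0.78 = 0.546; the absolute reading gives p2 = 0.48.

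**The plan's own figure, 200 couples, ICC 0**

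- Outcome 1, rate 2: 0.4/√(3.6/200) = 2.981; Φ(2.981 − 1.96) = 0.846.
- Outcome 2, relative: (0.154 − 1.96 × 0.04846)/0.04785 = 1.233; Φ = 0.891.

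So power above 0.80 is attainable at 200 couples when the ICC is low.

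**At the projected size, 88 couples, ICC 0**

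- Outcome 1, rate 2: 0.4/√(3.6/88) = 1.978; Φ(0.018) = 0.507.
- Outcome 2, relative: (0.154 − 1.96 × 0.07306)/0.07213 = 0.150; Φ = 0.560.

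| Couples | ICC | Outcome 1, rate 2 | Outcome 1, rate 4 | Outcome 2, relative | Outcome 2, absolute |
|---|---|---|---|---|---|
| 200 | 0 | 0.846 | 0.988 | 0.891 | 0.995 |
| 200 | 0.3 | 0.744 | 0.959 | 0.799 | 0.978 |
| 91 | 0 | 0.520 | 0.812 | 0.574 | 0.861 |
| 91 | 0.3 | 0.422 | 0.703 | 0.468 | 0.759 |
| 88 | 0 | 0.507 | 0.799 | 0.560 | 0.849 |
| 88 | 0.3 | 0.411 | 0.689 | 0.455 | 0.745 |
| 62 | 0 | 0.382 | 0.651 | 0.423 | 0.707 |
| 62 | 0.3 | 0.307 | 0.539 | 0.340 | 0.591 |

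Primary Analyses applies a Bonferroni correction to the separate 3- and 6-month models. Taking that as alpha 0.025 (replace 1.96 by 2.241), the 88-couple row at ICC 0.3 becomes 0.306, 0.584, 0.345 and 0.644.

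**Detectable reduction at 80% power, alpha 0.05, ICC 0 to 0.3** (the same formulas solved for power 0.80)

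| Couples | Outcome 1, rate 2 | Outcome 1, rate 4 | Outcome 2, from 70% |
|---|---|---|---|
| 200 | 19–21% | 13–15% | 13–15 points (19–22% relative) |
| 91 | 27–31% | 20–22% | 20–23 points (29–33% relative) |
| 62 | 33–37% | 24–27% | 25–28 points (35–40% relative) |

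**The case against.** The strongest reply is that a planning assumption and an interim count can both be true. The 200 couples are described as assumed, enrolment is described as ongoing, and the May 2025 end is itself projected. Entry depends on couples reaching the parent trial's 12-month visit, and the article shows neither the size nor the timing of that pool, so a constant monthly rate is an assumption. The figure of 62 rests on two couples between two counts dated only by month. All of this stands, and it limits the claim to what happens at the reported pace. It does not remove a fourfold gap for which the article offers no explanation.

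Stronger readings are tempting but not supported:

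- **The 200 couples cannot be reached.** The article does not show this; faster parent-trial flow or a later end date could change it.
- **The power calculation is wrong.** The stated figure is attainable at 200 couples under a low ICC and alpha 0.05. The problem is feasibility.
- **Power for outcome 1 collapses under overdispersion.** The analysis does name a negative binomial model, but no dispersion value is given. Much of any such loss would be present at 200 couples too, so it does not measure the enrolment shortfall.
- **The 200 is the number analysed, with no allowance for attrition.** The article does not say whether it means enrolled or analysed, and a condensed article may leave that to the full protocol.
- **A null result will be reported as no benefit.** Nothing in the article says so; the risk is that the text leaves that reading open.

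**Conclusion.** The concern holds as a conditional statement. At the reported pace and end date, enrolment would reach about 62 to 91 couples, under half of the 200 on which both power claims rest.

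At that size, power is below 0.80 in most of the cases examined. The exceptions at alpha 0.05 and ICC 0 are base rate 4 near the top of the range (0.80 at 88 couples, 0.81 at 91) and an absolute 22-point drop (0.85 and 0.86). Neither survives an ICC of 0.3 or a fall to 62 couples. At base rate 2, and under the relative reading of 22%, power never exceeds 0.58.

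The conclusion rests on steady accrual, a May 2025 end that is kept, no dropout, and an ICC and alpha that are assumed because the article states neither. A higher ICC, any dropout or the Bonferroni alpha would lower every figure.

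**What to change.** 1. Keep the 200-couple target on record as the planning figure.
2. Beside it, state the accrual projected by the randomization cut-off, as a range, with the expected flow of couples from the parent trial.
3. Restate power and detectable effects over that range, giving the ICC and alpha used and saying whether the 22% is relative or absolute. Alternatively, document how 200 will be reached, for example by a revised end date.
4. State before the outcome data are examined that, at the smaller size, a non-significant result will be read from the effect estimate and its confidence interval, not as evidence that retesting adds nothing.

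The cost of restating is wording, a registry update and a less favourable power figure. It needs no additional couples and no change to study procedures. Extending the end date instead would cost study time and the funding to cover it.
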